### Outcome measures

All participants in the study will be measured before the start of the study, after the intervention (3 weeks later), and again at a 6-month follow-up. A summary of all measurements in this trial is shown in Table 2.

**Table 2 Tab2:** Outcome domains and measurement instruments

Outcome domain	Measurement instrument	Abbreviation	T0	T1	T2

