**Secondary outcomes**					
MMT strength	MMT muscle strength grading standard	MMT	×	×	×
Motor function of lower limbs	Fugl-Meyer scale	FMA	×	×	×
Motor function	Motor function assessment scale	MAS	×	×	×
Ability of daily life activities	Improved Barthel index scale	ADL	×	×	×
Kinematic parameters of gait	Step with maximum knee angle		×	×	×
Time parameters	Total support time, step frequency		×	×	×
Distance parameters	Step length, pace, stride length		×	×	×

*T0* baseline, *T1* post-intervention (3 weeks), *T2* follow-up (6 months post intervention)

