### Sample size calculation

The sample size calculations are based on the primary outcome measure, the TUGT scale [35]. It was estimated that a sample of 28 participants (14 per group) would provide 80% power (*α* = 0.05, *β* = 0.2) to detect a difference between group means of 3.16. A difference of 3.16 points on the TUGT scale is regarded as minimum detectible change [36] using the program PASS, which takes into account the number of sample groups and the number of evaluation measures. To reach this total number of individuals, at least 36 individuals must be recruited, allowing a dropout rate of 20%.

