### Statistical analysis

SPSS statistical software will be used to build and process all data collected. Paired *t* tests will be used to evaluate the differences between group rehabilitation metrics before and after rehabilitation training. An independent sample *t* test will be used for measurement data between the groups. *P* < 0.05 is considered as the standard for significant difference. In addition, covariance analysis will be performed to adjust for any significant demographic or clinical imbalances. A safety analysis is scheduled after randomization and active treatment of 18 patients. Exploratory subgroup analyses may be conducted. To prevent data loss, all questionnaires will be user-friendly and collected electronically, with all study personnel trained to identify and engage subjects most likely to drop out of subsequent evaluations.

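### Covariance adjustment is tied to a significant baseline imbalance, so baseline TUGT is not a standing covariate and the between-group comparison gives up precision

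*Protocol article*

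**What the plan says.** The Statistical analysis section of the protocol article has three parts that bear on this point.

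- Within groups, paired t "tests will be used to evaluate the differences between group rehabilitation metrics before and after rehabilitation training". These use the baseline value but do not compare the arms.
- Between groups, an independent-sample t "test will be used for measurement data between the groups". The text does not say whether the data are post-treatment values or changes from baseline.
- In addition, "covariance analysis will be performed to adjust for any significant demographic or clinical imbalances". No covariate is named. The only significance threshold in the section is the preceding sentence: P < "0.05 is considered as the standard for significant difference".

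Baseline TUGT will be available for everyone. The Outcome measures section states "All participants in the study will be measured before the start of the study, after the intervention (3 weeks later") and again at 6 months, and Table 2 marks TUGT at T0, T1 and T2. TUGT is the primary outcome and the basis of the sample size. Randomization is 1:1, and no stratification by baseline walking ability is stated.

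**The concern.** In a randomized trial, a baseline significance test asks only whether chance produced a large difference. It does not ask whether the variable predicts the outcome. A covariate earns its place through its correlation with the outcome, and the baseline value of the same measure is usually the first candidate. Under the stated rule, baseline TUGT would be adjusted for in about 1 trial in 20 and left out of the model in the rest.

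Three things are at stake in a trial that plans on 28 evaluable patients: precision, a model fixed before the data are seen, and protection against a chance baseline difference too small to reach significance. The rule is stated in the protocol, so this is not a detail left to a later analysis plan.

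**Working it through.** **Inputs from the protocol (Sample size calculation).** Difference 3.16; 14 per arm evaluable; "would provide 80% power (*α* = 0.05, *β* = 0.2"); 20% dropout; 36 recruited.

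**Assumptions.** The test is two-sided. The outcome is normal with equal SD at baseline and follow-up. The baseline–outcome correlation r is not given, so it is shown at 0.3, 0.5 and 0.7.

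**Step 1: the plan's own figures.** Dropout: 14 / (1 − 0.20) = 17.5, rounded up to 18 per arm, or 36 in total. This agrees with the protocol. No SD is stated, so the 14 per arm cannot be reproduced independently. Solving the two-sample t-test power equation for 80% power with n = 14 and difference 3.16 gives SD = 2.87, a standardized effect of 3.16 / 2.87 = 1.10. The 80% for the unadjusted t test below is therefore built in.

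**Step 2: sensitivity of the trigger.** The smallest baseline difference significant at P < 0.05, in SD units, is t(0.975, 2n − 2) × √(2/n).

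- n = 14: 2.056 × 0.378 = 0.78 SD
- n = 18: 2.032 × 0.333 = 0.68 SD

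Under randomization this is reached in 5% of trials.

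**Step 3: what can remain in an unadjusted post-treatment estimate.** For a baseline difference just below the threshold at n = 14, the expected shift is r × 0.777 × 2.87.

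- r = 0.3: 0.67 (21% of 3.16)
- r = 0.5: 1.12 (35%)
- r = 0.7: 1.56 (49%)

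These are realised shifts given that imbalance, in either direction. They average to zero over randomizations.

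**Step 4: precision.** Residual variance relative to SD² is 1 for the post-treatment value, 2(1 − r) for the change score and 1 − r² for ANCOVA.

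| r | Post-treatment | Change score | ANCOVA |
|---|---|---|---|
| 0.3 | 1 | 1.40 | 0.91 |
| 0.5 | 1 | 1.00 | 0.75 |
| 0.7 | 1 | 0.60 | 0.51 |

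Since 2(1 − r) − (1 − r²) = (1 − r)², the ANCOVA variance is never larger than the change-score variance.

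**Step 5: power by simulation (100,000 trials per setting, 14 per arm, effect 1.10 SD).** The planned rule is taken as ANCOVA replacing the t test when baseline TUGT differs at P < 0.05.

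| r | t test, post values | Planned rule | t test, change scores | ANCOVA always |
|---|---|---|---|---|
| 0.3 | 80% | 80% | 66% | 82% |
| 0.5 | 80% | 81% | 80% | 89% |
| 0.7 | 80% | 81–82% | 95% | 97% |

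With all 18 per arm evaluable, the post-value t test has 89% and ANCOVA 91%, 95% and 99%.

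**Step 6: type I error at 14 per arm.** Over all randomizations the t test and ANCOVA both hold about 5%. The planned rule, read as replacement, is conservative: about 4.4% at r = 0.5 and 3.7% at r = 0.7. About 13.5% of trials have a non-significant imbalance above 0.5 SD. In those, the t test on post-treatment values rejects a true null about 9% of the time at r = 0.5 and 11% at r = 0.7, against about 5% for ANCOVA. Where the imbalance is below 0.4 SD, it rejects only about 2% at r = 0.7.

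**The case against.** The strongest case for the plan is that its test is sound. Three stronger readings might be inferred, and the documents support none of them.

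- **That the estimate is biased or false positives are inflated.** With 1:1 randomization the unadjusted t test is unbiased and holds 5%. The shifts in step 3 and the 9–11% in step 6 are conditional on an imbalance picked out after the fact, and they are offset by the low rejection rate in well-balanced trials. Read as replacement, the rule errs on the conservative side.
- **That the primary comparison certainly ignores baseline TUGT.** The text does not exclude a t test on change scores, which would use the baseline of every patient. At r = 0.7 that comes within about 2 percentage points of ANCOVA; at r = 0.3 it does worse than ignoring baseline.
- **That the trial falls short of its power target.** The sample size is for a difference in group means at 80% power, which fits an unadjusted comparison. The loss is relative to a better analysis of the same data.

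Two inferences must also be granted. The covariance analysis is introduced as an addition, so it may be meant to sit beside the t test; then the t test keeps its 5% level and the data do not select the primary model. And P < 0.05 is carried over from the adjacent sentence as the meaning of significant.

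What survives is that no reading makes baseline TUGT a pre-specified covariate, and no reading has more power than ANCOVA beyond rounding at the correlations shown.

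**Conclusion.** The point holds as one of efficiency and pre-specification, not of validity. Making adjustment depend on a significant imbalance is a poor rule: it is insensitive at this sample size, unrelated to prognostic value, and leaves both whether to adjust and for what to the data.

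Compared with a t test on post-treatment values at 14 per arm, always adjusting for baseline TUGT would gain about 2, 9 and 17 percentage points of power at r = 0.3, 0.5 and 0.7. Compared with a change-score t test the gains are about 16, 9 and 2 points. These sizes rest on the back-solved SD of 2.87, a two-sided test, normal data and an assumed r. The thresholds in step 2 rest only on n and on reading significant as P < 0.05.

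This should be fixed, but the trial's conclusions would not be invalid without it.

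**What to change.** In the Statistical analysis section, name one primary between-group model: ANCOVA of post-intervention TUGT time on treatment group and baseline TUGT, fitted whatever the baseline comparison shows, and reported as an adjusted mean difference with 95% CI. Use the same form at 6 months and for the continuous secondary outcomes, each with its own baseline value. Delete the significant-imbalance trigger. Keep the unadjusted t test as a sensitivity analysis and say whether it is on post-treatment values or change scores. Which of the two follow-up times leads for the primary outcome is a separate decision, because Table 2 does not rank them.

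The cost is one degree of freedom and no new data. The wording change does need a protocol amendment through the Scientific Board, with notice to the sponsor and funder, as the Protocol amendments section requires. It should be made before the analyst sees outcome data by group.

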### Study organization

This study will be organized and coordinated by researchers at the Department of Neurology of the union hospital affiliated with Fujian Medical University. Research staff will also oversee VR scene design and execution of clinically related experiments.

### Study oversight and participant confidentiality

The supervision of the project will be carried out by the safety supervision committee of the hospital, which is mainly responsible for the evaluation of the experimental design, the scientific and experimental process, the safety of participants, adherence to medical ethics, and the correct management and processing of data.

The privacy rights of each subject will be respected. All initial data and outcome indicators of participants will be kept in a highly secured database and anonymous work will be done to ensure the safety and rights of each subject.

### Safety

VR is an emerging technology and its related products have been gradually developed in recent years. To date, no relevant adverse events have been reported. In the process of training subjects’ gait recovery with VR technology; our research team will strictly follow the relevant regulations of the medical ethics committee to ensure the maximum safety and ethical protection of subjects. As VR technology is a relatively new technology, subjects may not be able to complete training tasks due to ineptness or intolerance (such as dizziness, nausea, sore eyes, disorientation) during training. Adverse events (e.g., falls, pain, and dizziness) that occur during the study period, whether or not related to the study intervention are registered. Considering the above two aspects, we will take the following measures to achieve the best training environment:
During the 3-week training, a strict training plan will be made for each subject on a weekly basis, adjusting the training schedule according to the actual conditions of the subjects;Pay close attention to the feedback and fitness of subjects using VR technology for rehabilitation training;Periodically evaluate the intervention effect of subjects using VR technology for rehabilitation training; andSupporting subjects’ decision to withdraw from the study.

This study will strictly comply with the requirements of clinical operation guidelines and internationally recognized legal requirements. Any adverse events will be reported directly to the ethics committee immediately, and the training regimen will be adjusted accordingly after each adverse event. There is no anticipated harm and compensation for trial participation.

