4. Procedures	The VR training group will receive (1) 30 min per day for 3 weeks (5 days/week) of VR-assisted gait rehabilitation training. Specific process of VR training: patients wear HTC Vive virtual glasses on the open ground and are synchronously equipped with different scenes such as nine-grid training, single-plank bridge training, climbing stairs training, and crossbar training. VR scenes are immersive. Patients are placed in virtual scenes and receive corresponding scores after completing tasks according to the training requirements of different scenes. (2) 30 min per day for 3 weeks (5 days/week) of regular active exercise training (unarmed drafting, muscle strength training, trunk balance, transfer).	The non-VR training group receives (1) 30 min per day for 3 weeks (5 days/week) of functional gait rehabilitation training (standing balance training, separation promoting exercise, center of gravity training, body position change training, step separation training, parallel bar walking training). (2) 30 min per day for 3 weeks (5 days/week) of regular active exercise training (unarmed drafting, muscle strength training, trunk balance, transfer).
5. Who provided	The intervention measures of the two groups in this study were carried out by rehabilitation therapists with over 3 years of experience. Intervention measures were developed by experimental researchers.	
6. How	Both interventions in this study will be conducted in one-on-one training sessions daily.	
7. Where	The intervention will be carried out in the inpatient ward of the Department of Neurology of the union hospital affiliated with Fujian Medical University.	
8. When and how much	During 3 weeks of rehabilitation training, both groups will receive training lasting 30 min/day and 5 days/week for 3 weeks. The intensity was adjusted immediately according to the gait function of patients’ lower limbs.	
9. Tailoring	The intervention of the two groups can be adjusted according to the gait function of patients. Before training, therapists will make a simple and rapid assessment of the lower limb function of patients to select the personalized intervention intensity suitable for patients. It can also be adjusted according to patients’ own preferences.	
11. How well	Evaluators overseeing intervention results will be blinded to the group allocation process and randomization results to ensure the objectivity and impartiality of the evaluation results.	

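### Two of the listed safety measures, close attention to feedback and periodic evaluation, are worded for VR users only, which risks unequal detection of adverse events between the arms

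*Protocol article*

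**What the plan says.** The protocol article's Safety section states the scope of adverse-event registration without reference to arm: "Adverse events (e.g., falls, pain, and dizziness) that occur during the study period, whether or not related to the study intervention are registered". It then lists four measures for the training period. The first covers everyone: "a strict training plan will be made for each subject on a weekly basis". The fourth, support for a decision to withdraw, refers to subjects in general. The second and third are limited by their wording to VR users: "Pay close attention to the feedback and fitness of subjects using VR technology for rehabilitation training" and "Periodically evaluate the intervention effect of subjects using VR technology for rehabilitation training".

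Three other places bear on the point:

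- Table 1, in the section on intervention design, gives both arms the same therapist contact ("Both interventions in this study will be conducted in one-on-one training sessions daily") and, under Tailoring, a check that applies to the two groups: "Before training, therapists will make a simple and rapid assessment of the lower limb function of patients".
- Outcome measures sets one assessment schedule for both arms: baseline (T0), the end of the 3-week training (T1) and the 6-month visit (T2).
- Randomization and blinding states that participants and the rehabilitation trainer cannot be blinded, while outcome assessors and the data analyst are.

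Statistical analysis schedules a safety analysis once 18 patients have been randomised and treated. It describes no between-arm test of adverse events.

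**The concern.** A register records only what is noticed. The events that the protocol names as examples are not specific to VR; they can occur in either arm soon after a stroke. Dizziness, pain and minor falls come to light largely because the patient mentions them or somebody asks. If closer attention to feedback is prescribed for one arm only, and the people giving and receiving the training know the allocation, the same event may be more likely to be recorded in that arm.

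The recorded events matter in three ways. They go to the ethics committee, they lead to an adjustment of the training, and they are the natural material for the safety analysis after 18 patients. Even without a formal test, adverse-event counts in a two-arm trial are read against the control arm. Data analysis cannot later restore events that were never noted.

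**Working it through.** The plan has no figure on this point to reproduce. The check is a comparison of wording, followed by an illustration of scale.

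**Wording, by scope**

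| Item | Where | Who is covered |
|---|---|---|
| Registration of adverse events | Safety | no limit by arm |
| Weekly training plan | Safety, first measure | every subject |
| Attention to feedback and fitness | Safety, second measure | VR users |
| Periodic evaluation of effect | Safety, third measure | VR users |
| Support for withdrawal | Safety, fourth measure | subjects in general |
| Daily one-on-one sessions | Table 1, How | both arms |
| Rapid check before training | Table 1, Tailoring | both arms |
| T0, T1, T2 | Outcome measures | both arms |

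The scope changes within a single list, and nothing elsewhere supplies a control-arm counterpart to the second and third measures. The check before training is shared, but it concerns lower-limb function and serves to choose intensity. It is not described as an enquiry about symptoms or tolerance. The timing, content, instrument and assessor of the periodic evaluation are not stated.

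**Illustration of scale (risk and detection are assumed; none is in the document)**

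Recorded risk = true risk × probability of detection. Spurious difference = true risk × (detection in VR − detection in control). The number per arm is 18, from the abstract. The true risk is set equal in both arms at 20%, 30% or 40%. Detection is 90% in the VR arm and 90%, 70% or 50% in the control arm.

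| True risk | Control detection | Recorded, VR | Recorded, control | Difference in patients | Risk difference |
|---|---|---|---|---|---|
| 20% | 90% | 18 × 0.20 × 0.90 = 3.24 | 3.24 | 0 | 0 points |
| 20% | 70% | 3.24 | 18 × 0.20 × 0.70 = 2.52 | 0.72 | 4 points |
| 20% | 50% | 3.24 | 18 × 0.20 × 0.50 = 1.80 | 1.44 | 8 points |
| 30% | 70% | 18 × 0.30 × 0.90 = 4.86 | 3.78 | 1.08 | 6 points |
| 30% | 50% | 4.86 | 2.70 | 2.16 | 12 points |
| 40% | 70% | 18 × 0.40 × 0.90 = 6.48 | 5.04 | 1.44 | 8 points |
| 40% | 50% | 6.48 | 3.60 | 2.88 | 16 points |

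The apparent risk ratio does not depend on the true risk: 0.90/0.70 = 1.29 and 0.90/0.50 = 1.80. If detection is equal, there is no spurious difference.

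If the 18 patients in the safety analysis are counted over both arms and split evenly, there are 9 per arm and the differences halve: 9 × 0.04 = 0.36 to 9 × 0.16 = 1.44 patients.

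**The case against.** The strongest reply is that the two VR-only items are tolerance precautions for a new device and not the method of ascertaining adverse events. They follow a description of VR intolerance and are introduced as ways to secure a good training environment. Registration itself is not limited by arm. Controls are inpatients seen one-on-one at each training session, so missing half of their events is a pessimistic assumption. The article also condenses a fuller protocol, and the way in which events are asked about is commonly left to that document or to the case report forms.

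Much of this stands. It removes any claim that bias is established, and it makes the upper end of the illustrated range hard to defend. The absence of a control-arm questioning procedure from the article is not the point either. What remains is wording that is present: one list assigns two measures to one arm and the rest to everybody. Shared therapist contact does not cancel extra attention prescribed for one side, and watching a new device closely does not require watching controls less.

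A reader might go further and infer that the VR arm receives extra assessments between visits, and that practice would then favour VR on the TUGT. The document supports neither step. The periodic evaluation may be nothing more than the common visits or the shared check before training, and no text uses the TUGT between visits.

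**Conclusion.** The point holds as a risk of unequal ascertainment. The Safety section, as worded, directs closer attention and periodic evaluation to VR users alone, in a trial where participants and trainers are unblinded and events are to be registered in all. If the wording is followed, adverse-event counts may not be comparable between arms, and the likely direction is against VR.

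The size cannot be derived from the document. The illustration runs from no excess to 2.9 recorded patients among 18 per arm, and it rests entirely on the assumed true risk and detection rates.

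It would be tempting to read this as a demonstrated bias in a planned comparison of adverse events. The text does not go that far: no such comparison is specified, and unequal detection is possible but not shown. No threat to the TUGT result, the sample size or the significance level follows. This is a cheap improvement and not a flaw in the primary analysis.

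**What to change.** Reword the second and third measures in the Safety section so that they cover all subjects. State that the same adverse-event and tolerance questions are put at each training session in both arms. VR-type symptoms such as sore eyes and disorientation can stay on the list and be asked of everyone. State that any interim evaluation uses the same method and schedule in both arms or, if the periodic evaluation means only the common visits or the check before training, say so. If a difference between arms is intended, give the reason and note that the event counts are then not directly comparable.

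The cost is about two lines of wording and a few minutes per control session for a therapist who is already present. None of the attention planned for VR users is reduced.
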